6.2 Dose Adjustments

M ETFORMIN

Patients will initially receive 1500 mg / day metformin for 7 consecutive days, and on day 8 they will be clinically evaluated for toxicity. Patients without evidence of serious adverse events (grade 3 or 4) will have metformin dose escalated to 2500 mg / day. In case of intolerance, the dose will be reduced to 1500mg / day. Dose reduction to 1000mg / day will be allowed in cases of grade 3 or 4 toxicity in patients taking metformin 1500mg / day, as well as dose reduction from 2500mg / day to 1500mg / day will also be permitted in cases of intolerance. .

Recovery of acceptable toxicity levels should occur within 3 weeks to allow further study. Those with toxicity that lasts for more than 3 weeks preventing re-introduction of the study drug will be excluded. Reduction of even metformin to level -1 will be allowed (table 1).

Table 1: Available dose levels for metformin.

| Level | Daily dose | Administration |
| --- | --- | --- |
| 1 | 2500 mg / day | 1 x 1500 mg  1 x 1000 mg |
| 0 | 1500 mg / day | 1 x 1000 mg 1 x 500 mg |
| - 1 | 1000 mg / day | 1 x 500 mg  1 x 500 mg |

Doses will be reduced for haematological and other adverse events. Dose adjustments are made according to the system that shows the highest degree of toxicity. Adverse events will be classified using the National Cancer Institute Common Terminology Criteria for Adverse Events Version 4 (NCI CTCAE). (73)

Table 2: Dose modifications for metformin-associated toxicities

| Toxicity | Grade 1 | Grade 2 | Grade 3 | Grade 4 |
| --- | --- | --- | --- | --- |
| Non hematologic | Keep the same  dose level | Maintain the same dose level. The dose may be discontinued until toxicity is ≤ 1 or has returned to baseline at the investigator's discretion. Then resume treatment at the same dose level. | Drop the dose until the toxicity is grade ≤ 1 or has returned to baseline, then resume treatment at the same dose level or reduce the dose to level 1 at the investigator's discretion **. | Drop the dose until the toxicity is grade ≤ 1 or has returned to baseline, then reduce the dose to level -  1 or discontinue treatment at the discretion of the investigator ^#^. |
| Hematologic | Keep the same  dose level | Maintain the same dose level *. | Discontinue the dose until the toxicity is ≤ 1 or has returned to baseline, then resume treatment at the same dose level ***. | Drop the dose until the toxicity is grade ≤ 1 or has returned to baseline, then reduce the dose to level 1 and resume treatment ^##^. |

* To start another cycle, the neutrophil count must be greater than 1,500 / mm ^3^, platelet count greater than 100,000 / mm ^3^and hemoglobin greater than or equal to 9 g / dL. ** Patients with grade 3 hypoglycemia, fatigue / asthenia who require more than 2 weeks without metformin administration to return to grade ≤ 1 toxicity should have their dose reduced to level -1.

*** Grade 3 lymphopenia and leukopenia do not require the dose to be suspended or reduced. Grade 3 recurrent neutropenia or thrombocytopenia that persists for at least 7 days requires dose reductions to level -1 in the next cycle.

Grade 4 haemorrhage requires discontinuation of study drug.

Grade 4 lymphopenia without other dose limiting events (opportunistic infection) does not require dose reduction.

If treatment discontinuation is required and the patient is unable to resume treatment within ≤ 28 days, treatment should be discontinued and the patient will continue to be followed for tumor response rate assessment and survival follow-up.

IRINOTECAN

Dose reduction in the patient will be allowed depending on the type and severity of the toxicity found. The dose levels of irinotecan are 125 mg / m², 100 mg / m² and 75 mg / m². The dose-limiting toxicities of irinotecan are related to neutropenia, alopecia, nausea, severe diarrhea, hypersensitivity reactions, asthenia and myalgia. Considering that the clinical toxicity most commonly related to irinotecan intolerance is diarrhea, the patient will be instructed to start treatment with loperamide when experiencing grade 1 diarrhea in order to avoid severe diarrhea and its complications.

| Toxicicity | Grade 1 | Grade 2 | Grade 3 | Grade 4 |
| --- | --- | --- | --- | --- |
| Non haematological | Keep the same dose level | Reduce dose in 25 mg/m²and on the next cycle keep the same dose level | Hold the dose until the toxicity is ≤ 2, then resume treatment with a reduced dose of 25 mg / m² (minimum dose of 75 mg / m2) | Hold the dose until the toxicity is ≤ 1 or has returned to baseline, then reduce the dose by 50 mg / m² (minimum dose 75 mg / m2)  or discontinue treatment, at the discretion of the investigator |
| Haematological | Keep the same dose level | Reduce dose in 25 mg/m² and on the next cycle keep the same dose level | ² Hold the dose until the toxicity is ≤ 2, then resume treatment with a reduced dose of 25 mg / m² (minimum dose of 75 mg / m2) | Hold the dose until the toxicity is ≤ 1 or has returned to baseline, then reduce the dose by 50 mg / m² (minimum dose 75 mg / m2)  or discontinue treatment, at the discretion of the investigator |

 DOSE SCALE

Every effort should be made to reschedule the metformin dose to the starting dose level. This applies to any of the dose reductions due to haematological or non-haematological toxicities. The dose should be rescheduled if the following criteria are met at least one month after dose reduction:

• All non-haematological toxicities Grade ≥ 2 reach Grade ≤ 1

• All Grade ≥ 3 hematologic toxicities reach Grade ≤ 1

• Or, alternatively, all haematologic toxicities and non-haematologica Grade ≥ 3 are resolved to a Grade ≤ 2 or can be controlled with supportive therapy.

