| Dose, treatment cycle | Metformin will be given at a dose of 1500mg/day (two pills in the morning at breakfast and one at dinner) for seven days. If there is no prohibitive adverse effect at 1500mg/day, the dose will be increased to 2500mg/day (three pills in the morning at breakfast and two at dinner), and this dose will be maintained until PD or unacceptable toxicity. Metformin will not be administered within two days prior to contrast infusion examinations at the discretion of the radiologist to minimize the risks of lactic acidosis.  Irinotecan will be administered at a dose of 125 mg/m² intravenously D1 and D8 every 21 days. |
| --- | --- |
| Preparation and administration | Metformin will have 500mg presentation. Not dosed by weight or body surface area. Irinotecan will be diluted in 5% dextrose solution. Its infusion will be performed intravenously, lasting 90 minutes. The irinotecan infusion will be preceded by the infusion of dexamethasone 20mg and ondansetrone 16mg. |
| Schedule of visits and evaluations | Study evaluations will be performed at the screening period (D-21 to D-1), the day of study initiation (D1), at D8 of the first cycle and at D1 of the subsequent cycles. |
| Effectiveness Assessments | Tumor assessment (CT or thoracic MRI, abdominal and pelvic) will be performed every 6 weeks until the 12^th^ week of initiation of treatment and after 12 weeks or at any time during the study where clinical progression is suspected. Any suspicion of progression due to clinical deterioration should be accompanied by radiological confirmation.  All images will be analyzed locally at the centers and this interpretation will be used for all clinical decisions. RECIST criteria will be used for primary endpoint analysis. |

1. Introduction

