This study will be conducted in Barretos Cancer Hospital. The tumor response will be evaluated in the sequence below, counting from the first day of medication infusion: 6th week, 12th week, 18th week, 24th week and every 12 weeks after, using consistent imaging techniques (CT) or MRI if patients are contraindicated for CT. The evaluation will be made by the researchers through RECIST v1.1. Discontinuation of metformin medication for three days prior to three days after infusion of any iodinated contrast media for radiological studies will be allowed at the discretion of the radiology team. This frequency of examinations is similar to that used in third-line mCRC clinical studies and arises from the need to follow more closely patients whose disease has more aggressive behavior and a greater chance of disease progression in the first few years.

Toxic effects will be analyzed according to NCI CTCAE version 4.0. (73)

The study period for each patient is defined as the day of patient inclusion until:

• The day when an event (disease progression as defined by RECIST, or death) is observed.

• The day when the patient discontinues treatment due to an unacceptable adverse event, withdrawal of consent or discontinuation of the study, or for any other reason than 21 days.

All those who discontinue treatment for any reason will be followed for survival assessment.

Patients who demonstrate disease progression during the study or who discontinue the study drug for any reason other than disease progression and withdrawal of consent (ie adverse event, administrative reasons, etc.) will be subjected to survival monitoring. The investigator or designated member will contact the patient monthly for survival information and additional antineoplastic therapies.

6. Therapeutic regimens, expected toxicity, dose modifications.

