6.1 Administration of medicines

Patients will be asked to take their metformin tablets daily twice a day at approximately the same time each day and should be instructed to swallow the whole tablets with a full glass of water, not chew them. All patients should avoid eating grapefruit during the study as this may increase and prolong exposure to the study drugs.  The vomited, missed or missed doses should not be re-administered and patients should take the next dose on time following the schedule. Interruption of metformin medication for three days prior to infusion of any contrast medium for radiological studies will be allowed at the discretion of the radiology team.

Metformin will initially be administered at a dose of 1500mg / day orally for 7 days, beginning on the first day of chemotherapy infusion. Patients with good tolerance (absence of grade 3 or 4 adverse events) may have metformin dose escalated to 2500 mg / day on the eighth day of the first cycle. This metformin dose and escalation regimen is in line with the current design of metformin research on cancer treatment, either alone or in combination with conventional chemotherapies. (25) These doses are the commonly used and recommended for the treatment of patients with diabetes. type II, whether they have cancer or not.

Patients will receive irinotecan 350 mg / m^2^ intravenously, diluted in 500 mL 5% dextrose solution, in continuous infusion lasting 3 hours on D1 every 3 weeks, exactly as is done in the routine care of this service. ( 75) Prior to irinotecan infusion, the patient will receive the following medications:

1. Dexamethasone 8 mg intravenously 15 minutes before infusion;

2. Ondansetron 8 mg intravenously 15 minutes before infusion;

3. Atropine 0.25 mg subcutaneously.

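### The haemoglobin entry limit, toxicity recovery limit, contrast hold and metformin dose-reduction levels each contradict another statement in the protocol and must be reconciled

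*Protocol*

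**What the plan says.** **Haemoglobin at entry.** The Synopsis inclusion criteria require at least 9.0 g/dL. Section 4.1 requires at least 10 g/dL and gives 5.6 mmol/L in brackets as the equivalent.

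**Recovery from toxicity.** The metformin text of section 6.2 sets a 3-week limit: "Those with toxicity that lasts for more than 3 weeks preventing re-introduction of the study drug will be excluded". The notes under Table 2, in the same section, set another for a patient "unable to resume treatment within ≤ 28 days, treatment should be discontinued".

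**Metformin hold around contrast.** The Synopsis (dose row) says "Metformin will not be administered within two days prior to contrast infusion examinations". Section 5 allows "Discontinuation of metformin medication for three days prior to three days after infusion of any iodinated contrast media". Section 6.1 allows "Interruption of metformin medication for three days prior to infusion of any contrast medium". All three leave the matter to radiology's discretion.

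**Metformin dose levels.** Table 1 in section 6.2 defines level 1 as 2500, level 0 as 1500 and level -1 as 1000 mg/day. In Table 2, the non-haematologic grade 3 cell says "resume treatment at the same dose level or reduce the dose to level 1" and the haematologic grade 4 cell says "then reduce the dose to level 1 and resume treatment". The non-haematologic grade 4 cell and the Table 2 notes refer to level -1 instead. The text before Table 1 says "Reduction of even metformin to level -1 will be allowed". It also gives steps in milligrams: from 2500 to 1500 for intolerance, and to 1000 for grade 3 or 4 toxicity in patients on 1500.

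**The concern.** These rules decide who enters, how long a patient may wait for toxicity to settle, how metformin is handled around each contrast scan, and what dose follows severe toxicity. In each case a clinician who follows one statement departs from another. Safety of the combination is a primary objective (section 3.1), so the toxicity results would describe patients managed under rules that the protocol does not fix. Eligibility also defines the 41 patients on whom disease control is counted. The contrast hold recurs, because imaging is every 6 weeks early in treatment and every 12 weeks later. The Synopsis links the hold to the risk of lactic acidosis, which section 1.2 calls the most serious potential adverse effect of metformin.

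**Working it through.** No planned sample size, power or error rate enters this point. The check sets the statements side by side, with a little arithmetic.

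1. **Haemoglobin.** Inputs: 9.0 g/dL (Synopsis); 10 g/dL and 5.6 mmol/L (section 4.1). Assumption, not in the protocol: monomer molar mass 16,114 g/mol, so 1 g/dL = 10/16.114 = 0.6206 mmol/L.
   - 9.0 × 0.6206 = 5.59 mmol/L
   - 10 × 0.6206 = 6.21 mmol/L
   - 5.6 / 0.6206 = 9.02 g/dL

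   The bracketed value fits the Synopsis limit, not the 10 g/dL beside it. For 5.6 mmol/L to equal 10 g/dL the factor would have to be 5.6/10 = 0.56, about 10% below the assumed one. For it to equal 9.0 g/dL the factor would be 5.6/9.0 = 0.622, within 0.3%. A patient at 9.5 g/dL (9.5 × 0.6206 = 5.90 mmol/L) passes the Synopsis limit and the bracketed limit but fails the 10 g/dL limit. The conflict between 9.0 and 10 g/dL needs no conversion factor. The 9 g/dL needed to start another cycle (Table 2 notes) is a separate rule and not part of the conflict.

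2. **Recovery limit.** 3 weeks = 3 × 7 = 21 days, against 28 days. The difference is 28 − 21 = 7 days. A patient who recovers on days 22 to 28 is off treatment under the first rule and may resume under the second. Both rules stand in section 6.2.

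3. **Contrast hold.** Excluding the day of the scan:
   - Synopsis: 2 days before, nothing stated after.
   - Section 5: 3 days before and 3 after, 3 + 3 = 6 days.
   - Section 6.1: 3 days before, nothing stated after.

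   Section 5 is limited to iodinated media; the other two are not.

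4. **Table 2 against Table 1.** Change in daily dose on moving to level 1 (2500 mg/day):
   - from level 1: 2500 − 2500 = 0
   - from level 0: 2500 − 1500 = +1000 mg (1000/1500 = +67%)
   - from level -1: 2500 − 1000 = +1500 mg (1500/1000 = +150%)

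   None is a reduction. Two of the four grade 3 and 4 cells are affected.

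5. **The same two cells with a minus sign restored.** Change on moving to level -1 (1000 mg/day):
   - from level 1: 1000 − 2500 = −1500 mg
   - from level 0: 1000 − 1500 = −500 mg

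   The second agrees with the milligram steps in the section 6.2 text. The first does not: that text takes a patient on 2500 to 1500 (−1000 mg) and names 1000 only for a patient already on 1500. Table 2 never names level 0 as a target.

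**The case against.** The strongest objection is that the two level 1 cells may not be in the sponsor's document at all. The adjacent non-haematologic grade 4 cell shows a minus sign separated from its digit, both affected cells use the verb reduce, and the notes attached to Table 2 speak of level -1. A sign lost in conversion would explain this, and it cannot be settled without the source file. That stands, and it limits what can be said about dose escalation. It does not remove step 5 or the other three conflicts. It can also be said that the milligram step from 2500 to 1500 is tied to intolerance without a grade, and that the general permission to go down to level -1 covers graded toxicity from any level. The protocol does not say so, and that is what needs clarifying.

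A reader might infer that the table raises the dose after severe toxicity in general. It does not: two of four cells are affected, one of them offers level 1 only as an alternative at the investigator's discretion, and a patient already on 2500 mg/day would see no change.

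A reader might also infer that patients described as excluded after 3 weeks leave the analysis, against the intention-to-treat principle. The protocol does not support this. The Table 2 notes keep patients who cannot resume in follow-up for tumour response and survival, section 11 follows excluded patients for survival, and sections 5 and 10.1 state intention-to-treat. Exclusion here reads as coming off treatment.

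Nor can it be claimed that sites would act differently. The Synopsis calls the study multicentric, but section 10.1 calls it single-centre and section 5 places it in one hospital. Finally, the contrast hold is discretionary in all three places, so the intervals are not mandatory durations. They still give radiology three different intervals to work from.

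**Conclusion.** The point holds as a set of contradictions in operative eligibility and safety rules. Their size is:

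- a 1 g/dL band of haemoglobin (9.0 to just under 10) in which eligibility is undetermined, with a unit error in section 4.1;
- a 7-day window (days 22 to 28) in which continuation of treatment is undetermined;
- three versions of a discretionary contrast hold, spanning 2, 3 or 6 days around the scan;
- two Table 2 cells whose target is the highest dose in Table 1 as printed, and which would still disagree with the section 6.2 text for a patient on 2500 mg/day if the target were level -1.

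The first three rest on the current text alone; only the unit mismatch uses an assumed conversion factor. The literal form of the fourth depends on the source file. No effect on the 9-of-41 decision rule or on any error rate is shown or claimed.

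**What to change.** Issue a protocol correction that reconciles:

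- the Synopsis inclusion criteria and section 4.1 on haemoglobin, with g/dL and mmol/L values that match;
- the 3-week and 28-day recovery limits within section 6.2;
- the Synopsis, section 5 and section 6.1 on the contrast hold, including whether it extends after the scan and which contrast media it covers;
- Table 2 with Table 1 and with the milligram steps in the section 6.2 text, after checking the two level 1 cells in the source file.

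The sponsor's clinicians choose every value; this review does not say which dose, interval or threshold is right. The cost is a text correction and its ethics committee approval, with no extra patients, visits or procedures.

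### Two cells of the metformin toxicity table order a reduction to level 1, which is the top dose of 2500 mg/day; level -1 was probably meant

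*Protocol*

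**What the plan says.** All of this is in protocol section 6.2, metformin part.

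- **Table 1** gives level 1 as 2500 mg/day, level 0 as 1500 mg/day and level -1 as 1000 mg/day.
- **Table 2, grade 3 non-haematologic:** hold until recovery, then, at the investigator's discretion, "resume treatment at the same dose level or reduce the dose to level 1".
- **Table 2, grade 4 haematologic:** hold until recovery, "then reduce the dose to level 1 and resume treatment". The cell offers no alternative. The notes below the table make exceptions for haemorrhage and for lymphopenia without other dose-limiting events.
- **Table 2, grade 4 non-haematologic:** after recovery, go to level -1 or stop.
- **Footnotes:** footnote ** sends slow-recovering grade 3 hypoglycaemia or fatigue/asthenia to level -1. Footnote *** reads "Grade 3 recurrent neutropenia or thrombocytopenia that persists for at least 7 days requires dose reductions to level -1 in the next cycle".
- **Text before Table 1:** everyone starts at 1500 mg/day for 7 days. On day 8, "Patients without evidence of serious adverse events (grade 3 or 4) will have metformin dose escalated to 2500 mg / day". For later reductions, "Dose reduction to 1000mg / day will be allowed in cases of grade 3 or 4 toxicity in patients taking metformin 1500mg / day", and "Reduction of even metformin to level -1 will be allowed (table 1").
- **Dose scale paragraph:** a reduced dose goes back up only when recovery criteria are met a month or more after the cut.

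**The concern.** The two cells use the verb for lowering a dose but name the level that Table 1 sets highest. An investigator who looks up level 1 in Table 1 finds 2500 mg/day. The rule fixes the metformin dose at restart after grade 3 or 4 toxicity, in a trial that lists the safety of the combination among its primary objectives (section 3.1).

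The grade 4 haematologic cell matters more, because it leaves no discretion: followed literally, it restarts the patient at the full dose. In the grade 3 non-haematologic cell the investigator can choose to resume at the same level, but the reduction offered as the alternative reduces nothing.

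**Working it through.** The protocol states no figure to reproduce. The check maps each entry to a daily dose through Table 1 and compares the results.

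**Inputs (Table 1):** level 1 = 2500, level 0 = 1500, level -1 = 1000 mg/day. The tablet splits agree: 1500 + 1000 = 2500, 1000 + 500 = 1500, 500 + 500 = 1000. The level labels in Table 1 therefore look sound, and the problem lies in Table 2.

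**Formula:** change = (new dose − current dose) / current dose.

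| Current dose | Cells as printed (level 1) | Cells with a minus sign (level -1) |
| --- | --- | --- |
| 2500 mg/day | (2500 − 2500)/2500 = 0% | (1000 − 2500)/2500 = −60% |
| 1500 mg/day | (2500 − 1500)/1500 = +67% | (1000 − 1500)/1500 = −33% |

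Two of the eight Table 2 cells are affected. As printed, neither can lower the dose from 2500 or from 1500.

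**The printed reading set against the other rules in 6.2:**

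1. *Escalation bar.* Only patients free of grade 3 or 4 events go to 2500 on day 8. Every patient is on 1500 in the first week. A grade 4 haematologic event in that week would, as printed, lead to a restart at 2500, which is the escalation that the same event rules out.
2. *Text on 1500 mg/day.* For grade 3 or 4 toxicity at 1500 the text allows a move down to 1000. The printed cells move the patient up.
3. *Footnote \*\*\*.* Persistent recurrent grade 3 neutropenia or thrombocytopenia goes to 1000. Grade 4 haematologic toxicity would restart at 2500, so the worse grade gets the higher dose.
4. *Restoration rule.* A reduced dose may rise again only after a month or more. The printed cells would raise it as soon as toxicity had fallen to grade 1 or baseline.

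**What was probably meant.** Level -1 appears in the adjacent grade 4 non-haematologic cell, in footnotes ** and ***, and in the sentence that permits reduction to that level. Restoring a minus sign in the two cells removes all four conflicts.

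**The case against.** The strongest reply is that this is a lost hyphen and not a flaw in the plan. The text does lose hyphens elsewhere: references 31 and 33 are the same article, and its page range is printed once without the hyphen and once with it. In the adjacent grade 4 cell there is a gap between the minus sign and the 1, as at a line break. The verb and the surrounding rules also point to level -1, so an attentive investigator would probably read the cells that way.

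Most of this stands, and level -1 is taken here as the likely intent. It does not remove the need for a correction. The minus sign survives in Table 1, in the neighbouring cell and in both footnotes, so the document carries two different labels that are both defined levels. The document also ends by naming a word-processor file as its source, which suggests, without proving, that the sign was lost in the sponsor's own text.

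Three stronger readings are tempting, and the protocol does not support them:

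- *That Table 2 wrongly omits a step from 2500 to 1500.* The text gives that step for intolerance ("dose reduction from 2500mg / day to 1500mg / day will also be permitted in cases of intolerance"). It also permits level -1 and nowhere requires a stop at level 0. Other Table 2 entries take a patient from 2500 straight to 1000 without conflict.
- *That the text contradicts itself on that step.* One sentence is directive ("In case of intolerance, the dose will be reduced to 1500mg / day") and the next is permissive. No consequence of the difference can be shown.
- *That the plan intends, or caused, full-dose restarts after severe toxicity.* The context argues against the intent, and the protocol gives no grade-specific rates from which to count patients. Both cells also hold metformin until recovery, and irinotecan has its own reduction rule for grade 4 events.

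**Conclusion.** Two Table 2 cells, grade 3 non-haematologic and grade 4 haematologic, are wrong as written. Taken literally, they give a 0% change from 2500 mg/day and a 67% increase from 1500 after grade 3 or 4 toxicity, and they contradict the other metformin rules in 6.2. The arithmetic rests only on the Table 1 levels. That level -1 was meant is an inference from the neighbouring entries; it is likely but not certain.

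The matter is one of safe and uniform dosing, and it should be corrected because the affected rule is an operative one. No effect on the sample size, the intention-to-treat denominator or the 9-patient threshold is claimed, and no number of affected patients is given.

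**What to change.** In Table 2, print *level -1 (1000 mg/day)* in place of level 1 in the grade 3 non-haematologic and grade 4 haematologic cells. Keep the grade 3 option to resume at the same level. Leave the grade 4 non-haematologic cell, footnotes ** and ***, and the 2500 to 1500 step for intolerance in the text as they are.

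Level 0 would be a poorer choice for the grade 4 haematologic cell. It would restart a patient from 2500 at 1500 mg/day, still above the 1000 that footnote *** sets for persistent recurrent grade 3 toxicity.

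The cost is a wording change in two table cells, made by protocol amendment after the investigators confirm the intended level. It adds no patients, visits or procedures.

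### The grade 2 cells of the irinotecan modification table have no minimum dose, so at 75 mg/m² they either lead to an unlisted 50 mg/m² or cannot be carried out

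*Protocol*

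**What the plan says.** All the relevant text is in Protocol section 6.2 (Dose Adjustments).

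- **Dose levels**, in the paragraph directly above the irinotecan table: "The dose levels of irinotecan are 125 mg / m², 100 mg / m² and 75 mg / m²".
- **Grade 2**, with the same instruction in the haematological and non-haematological rows: "Reduce dose in 25 mg/m²and on the next cycle keep the same dose level". Neither cell names a minimum.
- **Grade 3**, both rows: irinotecan is withheld pending recovery to grade 2 or lower. The cell goes on: "then resume treatment with a reduced dose of 25 mg / m² (minimum dose of 75 mg / m2" being the minimum printed in it.
- **Grade 4**, both rows: after recovery, "then reduce the dose by 50 mg / m² (minimum dose 75 mg / m2" being the minimum, or stopping treatment if the investigator so judges.
- **Cycle-start counts**, in a footnote to the grade 2 haematologic cell of the metformin table (Table 2): "To start another cycle, the neutrophil count must be greater than 1,500 / mm"³, with platelets above 100,000/mm³ and haemoglobin of at least 9 g/dL. The irinotecan table carries no such footnote.

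**The concern.** A dose-modification table should give one answer for each combination of current dose and toxicity grade. This one prints its minimum in all four grade 3 and grade 4 cells and omits it from both grade 2 cells. A site that follows the cells as printed could therefore reduce a patient further for a milder toxicity than for a more severe one, to a level outside the protocol's own list.

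Safety is part of the primary objective in section 3.1, and the trial has a single arm. Irinotecan dosing should therefore be reproducible from the text, so that the dose actually given, and the toxicity observed at it, can be described without having to guess how each investigator read the cell.

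**Working it through.** **Inputs.** Levels d = 125, 100 and 75 mg/m² and the cell rules, all from section 6.2. The grade 3 wording is taken as a reduction by 25, because a dose of 25 would contradict the 75 minimum in the same cell. Section 6.1 gives a different irinotecan dose and schedule. That is a separate discrepancy; the arithmetic here uses the levels that section 6.2 attaches to this table.

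**Formulas.**
- Grade 2 as printed: d − 25
- Grade 2 if the list is a floor: max(75, d − 25)
- Grade 3: max(75, d − 25)
- Grade 4: max(75, d − 50), or stop

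| Current dose | Grade 2 as printed | Grade 2, list as floor | Grade 3 | Grade 4 |
| --- | --- | --- | --- | --- |
| 125 | 100 | 100 | 100 | 75 or stop |
| 100 | 75 | 75 | 75 | 75 or stop |
| 75 | **50 (not listed)** | **75 (no reduction)** | 75 | 75 or stop |

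**Reading the last row.** As printed, 75 − 25 = 50, a cut of 25/75 = 33%, to a level absent from the list and below the 75 that follows grade 3. With the list as a floor, all three grades give 75 and the inversion disappears. The grade 2 cell then orders a reduction that cannot be made, and does not say whether to continue unchanged, hold or stop.

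**Closing clause of the grade 2 cell.** A patient at 125 goes to 100. The next cycle is 100 if the reduced level is kept, or 125 if the earlier level is meant. The paragraph on returning to the starting dose covers metformin only, and nothing in the protocol provides for raising irinotecan again. Keeping the reduced level is therefore the natural reading, but the cell does not state it.

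**Resuming versus starting a cycle.** The irinotecan table allows resumption after grade 3 haematological toxicity once it is grade 2 or lower. The footnote sets counts for starting a cycle. The protocol grades by CTCAE version 4 but does not reproduce its numerical limits, so the overlap can only be stated conditionally:
- If no part of the grade 2 range fails the footnote (neutrophils at or below 1,500/mm³, platelets at or below 100,000/mm³, haemoglobin below 9 g/dL), the rules never diverge.
- If part or all of the range fails it, the footnote blocks a new cycle in that part although the table would allow resumption.

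In either case both rules can be met together: hold until grade 2 or lower, and also meet the counts before a new cycle starts. On the synopsis schedule of days 1 and 8, a day 8 dose is not a cycle start, so the footnote does not address it.

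**The case against.** The best defence is that the three levels are listed immediately above the table. Read together, list and table provide no 50 mg/m² level, so a careful site would stop at 75 and no inversion would occur. Only patients who have already been reduced ever reach this situation, and the defect amounts to a missing parenthesis.

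Much of this stands. The list is a reasonable source for a floor, and nothing goes wrong at 125 or 100. It does not clear the grade 2 cell, for two reasons. The minimum was written into every grade 3 and grade 4 cell, so a reader may take its absence from both grade 2 cells as intended. And accepting the floor still leaves an instruction that cannot be carried out at 75, with nothing in its place.

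The defence is also right on the lesser points. Keeping the reduced level is the more natural reading of the closing clause, and the resumption and cycle-start rules are compatible.

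**Conclusion.** The point holds in a limited form. The grade 2 cells conflict with the dose-level list and with the grade 3 and grade 4 cells at one level, 75 mg/m². There the text yields either 50 (a 33% cut, unlisted, and below the dose after grade 3) or an instruction that cannot be followed. This rests only on the wording of section 6.2. The unclear closing clause and the unlinked count rule are secondary.

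A reader might infer more, but the protocol does not support it:

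- **That milder toxicity generally cuts the dose more than severe toxicity.** This happens only at 75, and only if the cell is read apart from the list.
- **That patients may be re-treated at counts the protocol forbids.** The footnote still governs any new cycle, and a conflict would depend on grade limits the document does not give.
- **That a stable abnormality present at entry would trigger repeated reductions.** Section 14.1 defines adverse events as occurring after study medication is given, and section 9 assesses study drug toxicity from the first dose. A worked example based on entry haemoglobin would also lean on a separate mismatch: 9.0 g/dL in the synopsis against 10 g/dL in the eligibility section (4.1).
- **That week-12 disease control is directly affected.** The protocol gives no basis for estimating how many patients would reach 75 mg/m² and then have grade 2 toxicity, so no effect on the primary endpoint is shown.

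**What to change.** Amend section 6.2 so that each combination of dose and grade has one answer:

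1. Reconcile the two grade 2 cells with the list of levels and with the minimum in the grade 3 and grade 4 cells, so that the instruction can be carried out at 75 mg/m².
2. State which level the closing clause of the grade 2 cell refers to.
3. Cross-refer the cycle-start count rule to the irinotecan table, and say how it works alongside the rule for resuming after a hold.

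The clinical team decides what the rules should be; this review proposes no dose or threshold. The cost is a wording amendment to one table and one footnote, with no extra patients, visits or analyses.
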